**Controlled interrupted time series (CITS)**

This CITS study will be conducted over 72 months and includes three distinct periods: a 49-month pre-intervention period (2020-2023), a 4-month intervention period and a 19-month post-intervention period (2024-2025). ITS is a quasi-experimental design for assessing public health interventions and is a robust method when other designs such as randomised controlled trials are impractical. ITS study designs allow adjustment of potential biases such as secular trends, seasonal trends, random fluctuations, and autocorrelation compared to other quasi-experimental designs such as controlled before and after studies.
^
34
^ Inclusion of a control group can strengthen an ITS evaluation by allowing assessment of whether any observed impact of the intervention is likely causal, or could instead be due to co-interventions or other events occurring concurrently with the intervention.

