**Intervention and control populations**

The social media campaign will be targeted to Aboriginal young people in the Perth region. The control group will be non-Aboriginal young people in the same location. We have chosen this characteristic-based control group because we expect that any co-interventions or concurrent events would likely affect both groups.
^
35
^ Therefore, if an impact is observed in both groups, this suggests it may be due to a co-intervention/concurrent event, while if the impact is only observed in the intervention series, this suggests the effect is more likely to be due to the intervention. During the intervention delivery we will collect information on events and interventions that occurred within Perth to improve HPV vaccination rates and who were the target population. We will report these in our final publication.

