**Data analysis**

*Interrupted time series*

A linear, segmented interrupted time series analysis will be used to evaluate the impact of the social media programme on HPV vaccination.

For the primary outcome, we will count the number of youths aged between 12 and before their 15
^th^ birthday who have received the HPV vaccination per month. Similarly, for the secondary outcome, we will count the number of young people aged up to 25 (inclusive) who have received the HVP vaccination per month. Our analysis models will include two segments: a pre-interruption period of 49 months, beginning on Jan 2020-Dec 2023, and a post-interruption period of 24 months, beginning on Jan 2024-Dec 2025, which encompasses both the intervention and post-intervention periods.

For each outcome, we will fit the following statistical model (Model 1), separately for the intervention and control series:

$$\text{Model}\;1:\log Y_{t}=\beta_{0}+\beta_{1}t+\beta_{2}I+\beta_{3}\left(t-T_{I}\right)I+\text{seasonal}+\text{offset}+\epsilon_{t}$$
where

$Y_{t}$
 is the outcome value at time t, and

$T_{I}$
 is the time of the interruption. The variable

I
 indicates the post-interruption segment, which is equal to 1 post the interruption and 0 before. Parameter

$\beta_{0}$
 is the intercept at the beginning of the series,

$\beta_{1}$
 is the slope in the first segment,

$\beta_{2}$
 is the level change between the expected value (based on the pre-interruption data) and the observed data, and

$\beta_{3}$
 is the difference in slope compared to

$\beta_{1}$
. The error term,

$\varepsilon_{t}$
 represents deviations from the fitted model, and we will assume these to have lag-1 autocorrelation. Seasonality will be accounted for by including two pairs of sine and cosine harmonics with periods of 12 and 6 months.
^
40,
41
^ Due to the changing of the vaccine schedule in the year following the interruption, the seasonal components will be phase shifted by six months for that year. The log of the relevant population (i.e. all Aboriginal youth aged between 12 and before their 15
^th^ birthday per month) will be included as an exposure offset to adjust for any changes to the population over time. We will assume a negative binomial distribution with a log link function. We will fit these models using the glarma package in R.
^
42
^

The effect measures of interest will be:

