•Level change at the end of the social media campaign (i.e. three months post the beginning of the social media campaign).•Change in slope.

In addition to the above model, for both outcomes, we will also fit the following single model (Model 2) that incorporates both the intervention and control series:

$$\text{Model}\;2:\log Y_{t}=\beta_{0}+\beta_{1}t+\beta_{2}I+\beta_{3}\left(t-T_{I}\right)I+\beta_{4}G+\beta_{5}\mathrm{tG}+\beta_{6}\mathrm{IG}+\beta_{7}\left(t-T_{I}\right)\mathrm{IG}+\text{seasonal}+\text{offset}+\epsilon_{t}$$
where

$Y_{t},T_{I},I,t,\text{seasonal},\text{offset and}\;\epsilon_{t}\;$
are as described above.

G
 represents the series with a value of 1 representing the intervention series, and a value of 0 representing the control series.

$\beta_{0}$
,

$\beta_{1}$
,

$\beta_{2}$
 and

$\beta_{3}$
 are as described above for the control series.

$\beta_{4},\beta_{5},\beta_{6}\;\text{and}\;\beta_{7}$
 represent the interactions between time and the intervention series. Specifically,

$\beta_{4}$
 represents the difference in the intercept at the beginning of the series between the intervention and control series,

$\beta_{5}$
 represents the difference in slope between the intervention and control series in the first segment,

$\beta_{6}$
 represents the difference in the level change between the intervention and control series, and

$\beta_{7}$
 represents the difference in the change in slope between the intervention and the control series.

We will compare the estimates of level change at the end of the social media campaign and change in slope between Model 1 and Model 2. This comparison will allow us to assess the possibility of whether a co-intervention/concurrent event may explain our findings.
^
35
^

We will plot interrupted time series graphs for all outcomes and series using the recommendations of Turner et al.
^
43
^ These plots will include: data points, trend lines, seasonality estimation and confidence intervals surrounding the trend line and counterfactual estimates. Segments will clearly delineated by breaks in the trend lines.

Subgroup analysis

We will fit Model 1 for the primary and secondary outcomes for the intervention series separately by:
•Sex (Females, Males)•Location in Perth (North West, North East, Central, South West and South East)

Influencer data

All qualitative information will then be synthesised descriptively, key messages will be identified, with thematic analysis completed using Nvivo software.

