### Dissemination

Part of the outcomes of this project will be a brand that will be associated with the HPV vaccine. It is expected this brand will organically be distributed amongst Influencers and their followers. We will also circulate the brand to health services and other organisations through collaborations with Aboriginal organisations. If this model is successful in improving HPV vaccination rates, the process of creating these improvements, the development of a public health model that engages young Aboriginal people to improve their health outcomes, will be easily translatable to other Aboriginal communities, health outcomes and populations. We will have developed a step-by-step guide on how to complete this, including branding that can be used by any young person or Influencer.

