### Study status

Intervention started Feb 2024.

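### The log of concurrent events covers only campaign delivery and only efforts to raise uptake, yet the change in slope is estimated over all of 2024-2025 and the control cannot reveal an Aboriginal-only event

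*Protocol article*

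**What the plan says.** Under Intervention and control populations, the protocol sets the scope of the event log: "During the intervention delivery we will collect information on events and interventions that occurred within Perth to improve HPV vaccination rates". It also records "and who were the target population. We will report these in our final publication". The same section chooses non-Aboriginal youth in Perth as the control because concurrent events are expected to reach both groups. It then treats an impact confined to the intervention series as pointing to the campaign.

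The section on the CITS design gives "a 4-month intervention period and a 19-month post-intervention period (2024-2025") after 49 months of pre-intervention data. Data analysis uses "a post-interruption period of 24 months, beginning on Jan 2024-Dec 2025, which encompasses both the intervention and post-intervention periods". The effect measures are the level change three months after the campaign begins and the change in slope. Of the comparison between Model 1 (each series alone) and Model 2 (both series), the protocol says: "This comparison will allow us to assess the possibility of whether a co-intervention/concurrent event may explain our findings".

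No section provides for collecting events after delivery, or events that would reduce uptake.

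**The concern.** Two safeguards separate a campaign effect from other causes: the control series and the event log. The control works for events that touch both groups. An event that reaches Aboriginal youth alone moves only the intervention series, and the Model 1 versus Model 2 comparison cannot distinguish it from the campaign. It enters the level and slope interaction terms of Model 2 (beta6 and beta7) directly. For such events the log is the only formal safeguard, and it does cover them while it runs, because it records the target population. But it ends with delivery, while the slope is estimated from data that run to the end of 2025.

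The limit to efforts meant to improve uptake leaves a second gap. A service disruption or adverse publicity affecting Aboriginal youth falls outside the log's scope, although it could hide a real benefit or look like harm from the campaign.

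What is at stake is the causal reading of a slope change seen only in the Aboriginal series.

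**Working it through.** **Month counts.** The CITS section gives 49 + 4 + 19 = 72 months. Data analysis gives "a pre-interruption period of 49 months, beginning on Jan 2020-Dec 2023" and a 24-month post segment, which sum to 73; January 2020 to December 2023 is in fact 48 months, and 48 + 24 = 72. How much of the post segment goes unlogged depends on what counts as delivery:

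- Four months, CITS section: 19 of 23 months unlogged (83%).
- Four months, Data analysis segment: 24 - 4 = 20 of 24 (83%). One of these 20 is January 2024, before launch ("Intervention started Feb 2024").
- Delivery running into term 3, as Stage 2 (Aim 2b) describes: fewer months, but still all of 2025, which is 12 of 24 (50%).

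**Size of the possible bias.** The protocol gives no figure for this, so event sizes are assumed. Setting: 72 months; intercept, trend, level change, slope change and two harmonic pairs (12 and 6 months) as in Model 1; AR(1) correlation 0.3 (the Sample size value); interruption at month 49 (January 2024) or month 50 (February 2024). The true campaign effect is set to zero. The event is y(t) = log(RR) in its active months and 0 otherwise, in the Aboriginal series only. Its generalised least squares projection on the model is b = (X'V⁻¹X)⁻¹X'V⁻¹y. False slope ratio per month = exp(b_slope). False level ratio at three months = exp(b_level + 3 × b_slope).

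| Assumed Aboriginal-only event | False slope change per month | Level ratio at three months |
|---|---|---|
| Sustained +10% from January 2025 | +0.6% | 0.993 to 0.997 |
| Sustained +20% from January 2025 | +1.2% | 0.987 to 0.994 |
| Sustained +10% from September 2024 | +0.5% | 1.020 to 1.025 |
| Sustained +20% from September 2024 | +1.0% | 1.04 to 1.05 |
| +10% in February to April 2025 only | +0.1% | 1.00 |
| +20% in February to April 2025 only | +0.2% | 1.00 |

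Worked line, +20% from January 2025, interruption at month 49: the level ratio at the interruption is 0.953 and the slope ratio 1.0117, so at three months 0.953 × 1.0117³ = 0.953 × 1.0355 = 0.987. With independent errors the same line gives 0.981, hence the bound of about 2%.

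The projection is linear in log(RR), so an event that divides uptake by 1.2 from January 2025 gives 1/1.0117 = 0.988, about -1.2% per month.

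These lines use unshifted harmonics. Adding the planned six-month phase shift for one post-interruption year leaves the slope for the January 2025 steps at about +0.6% and +1.1% to +1.2%.

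**Cost in precision of modelling an event.** Adding a step indicator to the same model multiplies the standard error of the slope change by about 1.5 (step in September 2024) to 1.9 (January 2025) at AR(1) 0.3, and by up to about 2.2 with independent errors.

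**The case against.** The strongest reply is that this is a condensed article and that procedures for logging events and sensitivity analyses belong elsewhere. That stands for the sensitivity model, whose absence is not counted here. It does not stand for the log: the article states its window and scope, and the words as written are too narrow.

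Several stronger readings are tempting, and the documents do not support them:

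- *The log covers exactly four months.* That section gives no number. Stage 2 has the campaign continuing to term 3 and starting again then, so delivery may be longer. Those passages need reconciling.
- *An Aboriginal-only event would be credited to the campaign.* The protocol's wording is tentative, and the Model 1 versus Model 2 comparison is only meant to assess a possibility. An event that lowers uptake would mask an effect, not be credited to it.
- *Nothing collected could show such an event.* The register data include provider location, timing and postcode; campaign posts are monitored for negative publicity; and the Aboriginal health council and the Cultural Governance Group will know the local setting. These are informal traces, not a dated log by target group.
- *Both effect measures are seriously biased.* For a January 2025 step the planned three-month level change barely moves. A level bias of 3% to 5% appears only if it is read at the interruption, which is not the planned measure.
- *The project's own brand circulation is a competing event.* The plan says "We will also circulate the brand to health services and other organisations through collaborations with Aboriginal organisations", but this is arguably part of the campaign. Its dates help interpretation; it is weak evidence of confounding.

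The slope figures also assume a lasting step. A short catch-up effort would do little.

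**Conclusion.** The point holds in limited form. The log's window and direction are too narrow for an effect measured over 2024-2025, and the chosen control cannot make up for this when an event reaches Aboriginal youth alone. The exposure is at least all of 2025 and, on the four-month reading, about 83% of the post-interruption months. The bias falls chiefly on the slope: about +0.6% or +1.2% per month for assumed sustained steps of 10% or 20% from January 2025, against +0.1% to +0.2% for a three-month pulse. The three-month level change moves about 2% or less for a January 2025 step and 2% to 5% for one from September 2024. Event sizes, shapes and dates are assumptions; nothing in the protocol shows that such an event occurred. This weakens the causal interpretation of a slope change and does not invalidate the design. It is worth correcting because the correction is cheap.

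**What to change.** In Intervention and control populations, replace the delivery window with the full evaluation period: at least January 2024 to December 2025, with earlier years compiled retrospectively where feasible. Record events expected to raise or to lower uptake, each with dates and target group (Aboriginal only, non-Aboriginal only, both). State that any slope change seen only in the intervention series will be interpreted against this log. Where a sustained Aboriginal-only event is logged after launch, add a sensitivity fit of Model 2 with an event-by-series indicator. Reconcile the campaign dates between Stage 2 and the CITS section so that the delivery period is unambiguous.

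Costs: modest logging work by existing staff and partners; recall error for past years; and one sensitivity fit per qualifying event. Each such fit will be imprecise, with a slope-change standard error about 1.5 to 2.2 times larger for steps between September 2024 and January 2025. It should therefore be reported as supportive only, since it will rarely separate event from campaign on its own.

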**Data collection**

Non-identifiable HPV vaccination data from the Australian Immunisation Register (AIR) will be requested from the Australian Institute of Health and Welfare (AIHW)’ National Health Data Hub.
^
36
^ Data will be requested for Aboriginal and non-Aboriginal people aged 12-25 years during 2020 to 2025 in the Perth region. Data from AIR will also include Aboriginal status, the timing of vaccinations, provider location, date of birth, address postcode and sex.

Analytics and information from Influencers delivering the campaign will also be collected to evaluate the campaign. We will also complete online or telephone interviews with the Influencers and managers of Influencers that have participated in our campaign to discuss the how they created content for the campaign, their ability to influence large audiences, and what worked and what could be improved in the process of working with the campaign. Influencers and managers will be provided with a $50 voucher for their participation in the interview.

**Outcomes**

The primary outcome, as defined by the World Health Organization and for reporting Australian reporting standards as a recipient of the HPV vaccination by the age of 15 years (ie before their 15
^th^ birthday).
^
37
^ Secondary outcome will be the number of young people who are the recipient of the HPV vaccination at 25 years old.
^
37
^

For Influencer analytics we will measure total number views, total likes, comments, and total shares. From our own social media platforms we’ll report on the average time each video was watched, whether a video was watched in full (percentage of viewers who watched the entire video), the source of where people found the videos and where the viewers were located.

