## Introduction

Human papillomavirus (HPV) is a common sexually transmitted infection that can lead to HPV-related cancers such as cervical cancer and other cancers such as anal, vaginal, and penile cancer.
^
1,
2
^ HPV rarely produces symptoms and cannot be cured or treated; therefore, vaccination is essential to protect against HPV and HPV-related diseases.

In 2007, Australia initiated the HPV vaccine through the National Immunisation Program (NIP) to girls aged 12 to 13 years in 2007 and to boys in 2013; catch up programs were implemented for older age groups. Up until 2023, the HPV vaccine provided as a free two-dose program for both males and females aged 12-13 years, with doses given between 5-6 months apart through school-based programs.
^
3
^ Responding to the global decline in HPV vaccination, lack of access to the vaccine and cost and burden required for two doses, WHO released updated recommendations in 2022 that a single dose was effective in reducing HPV.
^
4
^ As of 2023, Australia has transitioned to the single dose for 12-13 year olds through the NIP delivered at school with young people up to 26 years old also eligible for the free HPV vaccine. If a vaccine dose is missed at school, depending on their place of residence, a young person may receive a free catch-up dose at their school, their local Aboriginal or government health centre, or private general practitioner.

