**Sample size**

Based on data from the Australian Bureau of Statistics, we anticipate approximately 89 Aboriginal youth turning 15 years old each month in Perth over the study period.
^
32
^ Using the primary outcome definition, monthly numbers of young people before their 15
^th^ birthday fully vaccinated against HPV, will be the unit of aggregation in the regression models. A total of 72 monthly data points (2020-2025) will provide 85% power to detect a one-standard-deviation shift in the average proportions post-intervention, at an α = 0.05 and a first-order autoregressive model with autocorrelation of 0.3.
^
38
^ Empirical research has shown autocorrelations of the order of 0.3 (median 0.33; IQR 0.03, 0.58; 36 ITS studies in public health).
^
39
^

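### The primary outcome is three different quantities across Outcomes, Sample size and Data analysis, and the 85% power does not apply to the level change that Model 1 will estimate

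*Protocol article*

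**What the plan says.** All places are in Stage 3 of the protocol article unless stated.

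- **Outcomes** defines the primary outcome "as a recipient of the HPV vaccination by the age of 15 years", meaning before the 15th birthday, and ties it to WHO and Australian reporting standards.
- **Sample size** takes its monthly number from a birthday cohort: "we anticipate approximately 89 Aboriginal youth turning 15 years old each month in Perth over the study period". It then says that monthly numbers before the 15th "birthday fully vaccinated against HPV, will be the unit of aggregation in the regression models", and claims "85% power to detect a one-standard-deviation shift in the average proportions post-intervention" with 72 monthly points, α = 0.05 and first-order autocorrelation of 0.3.
- **Data analysis** says "we will count the number of youths aged between 12 and before their 15"th birthday who have received the vaccine per month. The offset is set as follows: "The log of the relevant population (i.e. all Aboriginal youth aged between 12 and before their 15"th birthday per month). The model is negative binomial with a log link, a trend, a level change, a slope change and seasonal harmonics. The effect measures are the level change three months after the campaign begins and the change in slope.
- **Data collection** requests records for "people aged 12-25 years during 2020 to 2025 in the Perth region".
- **Study status** dates the start of the intervention to February 2024.

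**The concern.** These sections should describe one primary outcome. The first is an attained status, the second a coverage proportion in those reaching 15 in a given month, and the third a count or rate over a three-year age band. They respond to a campaign at different speeds and have different denominators.

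Sample size also speaks of being fully vaccinated, whereas Outcomes and Data analysis speak only of receiving the vaccine. The Introduction says "As of 2023, Australia has transitioned to the single dose for 12-13 year olds", so full vaccination changes meaning inside the pre-intervention period.

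Two things are at stake. A modelled monthly rate could be reported as if it were WHO coverage at 15, or the choice between them could be made after the data are seen. And readers would rely on a power figure that belongs to a simpler contrast than the one to be tested.

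**Working it through.** **1. The quantities side by side**

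| Section | Unit | Denominator |
|---|---|---|
| Outcomes | vaccinated or not by the 15th birthday | not stated |
| Sample size | proportion, apparently of those turning 15 in the month | about 89 |
| Data analysis | monthly count over ages 12 to under 15 | the whole age band |

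Size of the age band, assuming equal birth-month cohorts:
- From the 4983 people aged 12-16 (Setting and target population): 4983 / 60 = 83.05 per birth month; × 36 = 2,990.
- From the 89 per month: 89 × 36 = 3,204.
- Ratio to 89: 2,990 / 89 = 33.6, and 3,204 / 89 = 36.

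**2. The stated power**

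Inputs: 72 months, split 48/24 (January 2020 to December 2023, then January 2024 to December 2025); ρ = 0.3; a shift of 1 marginal SD; two-sided α = 0.05 (sidedness is not stated). With V the AR(1) correlation matrix and X the design matrix, SE is the square root of the relevant diagonal element of (X′V⁻¹X)⁻¹, and power = Φ(1/SE − 1.96).

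With X holding only an intercept and the post-period indicator, SE = 0.332, 1/0.332 − 1.96 = 1.05, and power is **85.4%**. The text counts the pre-period as 49 months; a 49/23 split gives 84.6% and 49/24 gives 85.6%. So the stated 85% is reproduced as a step in the mean with no time trend.

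**3. The same inputs with Model 1's terms**

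X now holds intercept, trend, level change and slope change.

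| Contrast | SE | 1/SE − 1.96 | Power |
|---|---|---|---|
| Level change at the interruption | 0.622 | −0.35 | 36% |
| Same, with 12- and 6-month harmonics | 0.646 | −0.41 | 34% |
| Level change three months in | 0.578 | −0.23 | 41% |
| Same, with harmonics | 0.598 | −0.29 | 39% |

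For 85% power the shift must be (1.96 + 1.036) × SE. That is 2.996 × 0.578 = 1.73 SD at best and 2.996 × 0.646 = 1.94 SD at worst, against the planned 1 SD.

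**4. Calendar, if the series were indexed by month of 15th birthday**

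- A child aged 12 on 1 February 2024 turns 15 between February 2026 and February 2027. None does so by December 2025.
- February 2024 to December 2025 is 11 + 12 = 23 months. Of the 36 birth-month cohorts aged 12-14 at launch, 23 enter the series and 36 − 23 = 13 do not.
- The 23 enter with 0 to about 22 months of exposure, so the effect builds up gradually. At the three-month effect measure, those turning 15 were already about 14 years 9 months old at launch.

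**5. The same question under the count in Data analysis**

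If the count means new vaccinations in the month, a 12-year-old vaccinated in 2024 registers at once and step 4 does not apply. The wording does not say whether it means new vaccinations or all those already vaccinated.

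**The case against.** The sections can be read in sequence as definition, aggregation and model. Sample size itself says that it uses the primary outcome definition and that monthly numbers enter the regression, and Outcomes never says that the series is indexed by birthday. The harmonics and the six-month phase shift for the changed vaccine schedule also fit dosing by calendar month better than coverage by birthday. This has force: Data analysis is the operational text. It does not explain why the sample size rests on those turning 15 and on proportions.

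Several stronger readings are tempting, and the documents do not support them:

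- **That the primary outcome cannot register the children the campaign is aimed at.** This holds only for 12-year-olds at launch, and only under birthday indexing. Even then 23 of 36 cohorts (64%) enter, and the campaign also targets ages up to 16 and catch-up doses.
- **That the 34- to 36-fold denominator gap undermines the 85%.** The effect is set in SD units and the figure reproduces without either denominator. The gap changes what one SD means in practice. The shortfall in power comes from the trend and slope terms.
- **That dose histories are cut off at 2020.** The data request may restrict the people rather than the dose dates, and it lists the timing of vaccinations. This needs confirming.
- **That Model 1 already analyses first vaccinations.** The text says neither first nor new.

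**Conclusion.** The point stands. The primary outcome is not fixed as one quantity, and the quoted power belongs to a trend-free step in the mean (85.4%), not to the level change in Model 1 (about 34% to 41% on the same inputs). The first part rests on the text alone. The second assumes a two-sided test, a shift in marginal SD units, the 48/24 split and a Gaussian AR(1) approximation to the negative binomial model. It shows that the stated figure does not carry over; it is not a forecast of the study's true power, because the SD has no numerical value in the article. The six-month phase shift was not modelled.

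The timing problem is conditional: under birthday indexing the effect is diluted and delayed, but the series is not empty of exposed youths. Under a count of new vaccinations it does not arise.

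**What to change.** 1. In Outcomes, state that the primary outcome is the monthly rate of new (first recorded) HPV vaccinations among Aboriginal youths aged 12 to under 15. Say explicitly in Data analysis that the count is of first recorded vaccinations in the month, with the existing offset.
2. In Sample size, replace the 89 turning 15, the proportions and the fully vaccinated wording with that rate and denominator. Give the power for the effect measures Model 1 will report: the level change three months in and the change in slope, with trend, harmonics and autocorrelation included.
3. Report WHO coverage at 15 descriptively, noting that children aged 12 at launch turn 15 only after the data end.
4. Confirm that the data request includes doses given before 2020. They are needed both to identify first doses and to compute coverage.

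The cost is wording, a power calculation and a clarification of the data request; the campaign is unaffected. The downside is that the headline outcome is no longer the WHO indicator and the stated power becomes less favourable.
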